### Criteria for discontinuing or modifying allocated interventions {11b}

As randomization takes place during the procedure, the patients can accept inclusion but be excluded during the proposed intervention if the identified arterial lesion is not confirmed to be significant by intraoperative pressure measurement or multiplane angiography. If a patient is excluded perioperatively, the operator will make a determination on whether the procedure continues according to standard treatment or if an alternative approach is deemed necessary.

The patient has the right to withdraw participation at any time without providing a reason. In the event of refusal or withdrawal, the patient will be transitioned to the standard care pathway for treatment.

### Strategies to improve adherence to interventions {11c}

All patients included in the COMESS trial will be followed up with clinical exam, blood samples, DUS of the visceral arteries, and QoL questionnaire at 6 weeks, 12 months, and then annually to 5 years postoperatively. During this time, information from exams, tests, and information will be gathered. CTA is performed at 12 months and will be done at the local hospital.

### Relevant concomitant care permitted or prohibited during the trial {11d}

There is currently no concomitant care that is prohibited during the trial. At the point of discharge from the hospital, patients will be prescribed statins and relevant antiplatelet therapy, already on other pertinent anticoagulant therapy.

### Provisions for post-trial care {30}

Patients are covered by general patient insurance (patienterstatningen).

## Outcomes {12}

### Primary endpoint

Primary stent patency at 1 year (< 50% stenosis)

### Secondary endpoint(s)—evaluated at 12 months and 5 years

Secondary stent patencyFreedom from stent re-stenosis (luminal diameter > 50%)Freedom from reinterventionOverall survivalIntervention free survivalFreedom from symptom recurrenceProteomics assay signal (balloon) and concentration of established biomarkers (blood samples)Quality of lifeSensitivity and specificity of CTA and US preoperatively and during follow-up

### Participant timeline {13}

See Tables 1 and 2.

**Table 1 Tab1:** Standard participant timeline

Enrolment	Baseline	6-week follow-up	12-month follow-up	2-year follow-up	3-year follow-up	4-year follow-up	5-year follow-up
Informed consent	X						
EQ-5D-5L	X	X	X	X	X	X	X
SF-36	X	X	X	X	X	X	X
Medical history	X						
Physical examination	X	X	X	X	X	X	X
CT-angiography	X		X				
Duplex ultrasound	X	X	X	X	X	X	X

**Table 2 Tab2:** Modified participant timeline

Enrolment	Baseline	6-week follow-up	12-month follow-up	2-year follow-up	3-year follow-up	4-year follow-up	5-year follow-up
Informed consent	X						
EQ-5D-5L	X	X	X	X	X	X	X
SF-36	X	X	X	X	X	X	X
Medical history	X						
Physical examination	X	X					
CT-angiography	X		X				
Duplex ultrasound	X	X					
Telephone consultation		X	X	X	X	X	X

### Sample size {14}

In the only study investigating CS vs BMS in CMI [10], a retrospective non-randomized study of 225 patients, patients treated by CS had freedom from restenosis of 92% ± 6% compared to BMS with freedom restenosis of 53% ± 4% [10]. This study suffered several limitations that must be considered for a sample size estimation in the present RCT: the velocity cut-off used may overestimate high-grade restenosis, the follow-up was significantly longer in the BMS group, and differences in time-dependent outcomes including restenosis must be expected. In addition, a general underreporting of outcomes in both the BMS and the CS arm must be expected in a retrospective study. Therefore, the expected restenosis rates were adjusted to 85% and 60%.

Using dichotomous endpoints (restenosis: Y/N), a two independent sample study, alpha = 0.05, beta = 0.2, and power = 0.8, sample size was estimated to 49 patients in each group (total = 98). With 120 CMI/AoCMI patients treated yearly in Copenhagen, an estimated inclusion rate of 80% and 20% dropout, a total of 77 CMI patients will be randomized yearly (app 6 pts/month)—and 98 patients are expected included within 18–24 months.

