**Methods:**

This is an investigator-driven, prospective, randomized, single-blinded, and single-center, national cohort study at the Copenhagen University Hospital, Denmark. A total of 98 patients with chronic mesenteric ischemia (CMI) and acute-on-chronic mesenteric ischemia (AoCMI) will be randomized to treatment with either BeSmooth BMS (Bentley Innomed GmbH) or BeGraft CS (Bentley Innomed GmbH). Randomization occurs intraoperatively after lesion crossing.

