### Trial design {8}

This is a single-blinded, single-center, national, prospective, randomized controlled trial comparing covered stents and bare metal stents in the treatment of mesenteric vessel stenosis in patients with CMI. The COMESS trial is a superiority trial, with two parallel groups and a primary end point of primary stent patency at 1 year. Randomization is done as block randomization with a 1:1 allocation ratio.

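### The 98 patients to be randomised are the no-loss number: the 20% dropout enters only the accrual figure, so the stated 80% power requires a 12-month result from every randomised patient

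*Protocol article*

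**What the plan says.** The calculation is in the protocol article, Sample size {14}. The design is binary: "Using dichotomous endpoints (restenosis: Y/N), a two independent sample study". The rates are introduced with "the expected restenosis rates were adjusted to 85% and 60" (per cent). They come from freedom-from-restenosis figures, and the calculation is the same whichever way they are labelled. The error rates are "alpha = 0.05, beta = 0.2, and power = 0.8", and the result is "sample size was estimated to 49 patients in each group (total = 98". Dropout plays no part in that step.

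The 20% appears in the next sentence, on accrual, which starts from 120 CMI/AoCMI patients treated a year: "an estimated inclusion rate of 80% and 20% dropout, a total of 77 CMI patients will be randomized yearly".

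The Methods paragraph of the abstract confirms that 98 counts patients randomised, not patients with a result: "A total of 98 patients with chronic mesenteric ischemia (CMI) and acute-on-chronic mesenteric ischemia (AoCMI) will be randomized". Allocation is equal: "Randomization is done as block randomization with a 1:1 allocation ratio" (Trial design {8}).

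Several other sections allow for randomised patients whose primary result may be missing:
- Criteria for discontinuing {11b}: "The patient has the right to withdraw participation at any time without providing a reason".
- Plans to promote retention {18b} returns patients who leave after randomisation to standard care.
- Section {20c} plans for missing data without imputation.
- Overall survival at 12 months is a secondary endpoint.

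**The concern.** The protocol states a dropout rate next to its sample size but does not carry it into the sample size. A reader who sees 80% power and 20% dropout in consecutive sentences will assume that the 98 covers the dropout. It does not.

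The primary endpoint is patency at 1 year in a superiority trial. The protocol's Discussion presents the trial as important for deciding which stent to use, in a field without prospective controlled data. If some randomised patients have no 12-month result, the design does not deliver its stated power. A null result would then be read as coming from an 80%-powered trial although the chance of missing the planned difference was above 20%.

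**Working it through.** **Inputs.** From Sample size {14}: p1 = 0.85, p2 = 0.60, alpha = 0.05, power = 0.80, 49 per arm, 120 patients a year, 80% inclusion, 20% dropout. From Trial design {8}: 1:1 allocation. Assumed: a two-sided test, because the protocol does not state sidedness.

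**Step 1: reproduce the plan's figure.** Pooled two-proportion formula without continuity correction:

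n per arm = [z(0.975) × √(2p̄q̄) + z(0.80) × √(p1q1 + p2q2)]² / (p1 − p2)²

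- p̄ = 0.725, so 2p̄q̄ = 2 × 0.725 × 0.275 = 0.39875, square root 0.6315
- p1q1 + p2q2 = 0.1275 + 0.2400 = 0.3675, square root 0.6062
- n = (1.960 × 0.6315 + 0.8416 × 0.6062)² / 0.0625 = 48.88, rounded up to 49

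The plan's 49 is reproduced exactly, with no inflation. Power at 49 per arm is 80.1%.

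**Step 2: find where the 20% is used.** 120 × 0.8 = 96, and 96 × 0.8 = 76.8, the stated 77 randomised a year. The 20% is used up there. No section adds patients for missing 12-month results.

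**Step 3: power when some randomised patients have no 12-month result.** With n evaluable per arm:

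power = Φ{[0.25 × √n − 1.960 × 0.6315] / 0.6062}

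| Share without a 12-month result | Evaluable per arm | Power |
|---|---|---|
| 0% | 49 | 80.1% |
| 5% | 46.6 | 78.0% |
| 10% | 44.1 | 75.7% |
| 15% | 41.7 | 73.2% |
| 20% | 39.2 | 70.6% |

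The 20% row is 98 × 0.8 = 78.4, about 78 evaluable patients. It depends a little on method: pooled 70.6% (70.3% at 39 per arm), arcsine 72.0%, unpooled 73.3%, and 72.3% from an exact calculation for the chi-square test at 39 per arm. The range is thus about 70% to 73%.

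**Step 4: what 39 per arm can detect.** With 60% in one arm, 80% power needs about 87.5% in the other, a difference of 27.5 points in place of 25. The half-width of the 95% confidence interval for the difference, 1.96 × √(0.3675/n), grows from 17 points at n = 49 to 19 points at n = 39.

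**The case against.** The strongest objection is to the 71%. A reader might infer that the trial has only about 71% power because the protocol itself expects 20% dropout. The text does not support that. Its arithmetic takes the 20% off to arrive at patients randomised per year, that is, before randomisation. The trial has such a loss: consented patients can be excluded on the table if the lesion is not confirmed as significant ({11b}), and randomisation follows only after the lesion is crossed and judged significant ({16c}). On this reading the 20% is in its right place and should not be applied again to the 98. This part of the objection stands. It makes the 71% one point on a range, but it does not supply an allowance for loss after randomisation.

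Nor does the protocol give any figure for withdrawals or deaths before 12 months. Its remark on high mortality concerns acute mesenteric ischemia, which is excluded. The size of any loss is therefore an assumption.

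Three further points can be made.
- A one-sided test needs 39 per arm, and 39/0.8 = 48.75 also rounds to 49, so the figure could in principle include inflation. The protocol states neither a one-sided test nor any inflation, and the two-sided uninflated formula gives 49 directly.
- Section {20a} also names survival analysis for the primary outcome. That would use part of the follow-up of patients who leave and might lose less power. The sample size was nevertheless set for a binary endpoint.
- Loss is already limited in part. The 12-month CTA is done at the local hospital, the modified timeline keeps it, and patients who leave return to standard care with DUS at 12 months. What is not stated is permission to use those routine results.

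**Conclusion.** The point holds in a conditional form. Both of the plan's calculations, 49 per arm and 77 a year, are correct as arithmetic. The fault is that 98 is the number randomised and also the number that must be evaluable for 80% power, while the one dropout figure given is used only for accrual. This is so whichever way the 20% is read: if it is loss after randomisation, it was left out of the sample size; if it is loss before randomisation, nothing is allowed for afterwards.

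The cost in power is about 2 points at 5% loss and just under 10 points at 20% loss (80.1% to 70.6%). These figures rest on a two-sided test, the binary endpoint, the planned rates of 85% and 60%, and equal loss in the two arms. The documents do not support a flat statement that the trial has 71% power, nor one that the protocol expects 20% of randomised patients to be lost.

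**What to change.** In Sample size {14}:

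1. State whether the 20% is loss before or after randomisation, and state the sidedness of the test.
2. Restate the power with its condition, for example:

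> With 98 patients randomised, power is 80% only if 12-month data are complete. If 5%, 10%, 15% or 20% of randomised patients lack a 12-month result, power is about 78%, 76%, 73% or 71% (pooled two-proportion formula; about 70–73% at 20% loss, depending on the approximation). At 20% loss, the difference detectable with 80% power is about 27.5 points (87.5% against 60%).

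3. Ask patients who leave study visits for permission to use their routine 12-month imaging. Section {18b} says that standard care already includes DUS at 12 months, so this adds no examination and reduces the number of lost primary outcomes.

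The cost is a less favourable stated power and a sentence on routine imaging; no extra patients are required. If the sponsor instead wished to hold 80% power at 20% loss, 49/0.8 = 61.25, so 62 per arm (124) would be needed. At the protocol's own 76.8/12 = 6.4 patients a month this takes 124/6.4 = 19.4 months, within the stated 18 to 24. Enrolment began in June 2023, so restating the power may be the more practical course.

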### Recruitment {15}

Patients are discussed in a multidisciplinary team (MDT) at Copenhagen University Hospital (Rigshospitalet) in Denmark, including vascular surgeons and interventional radiologists after the referring physician has ruled out other gastrointestinal causes. If a consensus decision of CMI or AoCMI is reached and the diagnostic workup and clinical findings support endovascular treatment, the patient is invited to participate in the study.

## Assignment of interventions: allocation

### Sequence generation {16a}

The process of randomization is done in Research Electronic Data Capture (REDCap). Randomization will be in block sequence to get equal patient allocation in the two treatment arms in REDCap, a third party electronic dataset system, and accessible only to the physician/research nurse/coordinator performing the randomization. Only the treating team will know the allocation (CS vs BMS).

### Concealment mechanism {16b}

Randomization is done in REDCap, a password secured third party database, and is only accessible to those whom have been granted access to the project.

### Implementation {16c}

Eligible patients and the eventual next of kin will have oral and written information about the project by a project responsible physician or project nurse. As noted previously, randomization is done in Research Electronic Data Capture (REDCap), after the patient has provided informed consent. Randomization will be performed on an intention-to-stent basis in the angiosuite once the target lesion has been crossed with a guidewire and the lesion is determined clinically significant by angiography (> 50%) or pressure measurement (> 15 mmHg mean gradient). Only the treating team will know the allocation (CS vs BMS).

## Assignment of interventions: blinding

### Who will be blinded {17a}

This is a single-blinded study. Patients and the physicians responsible for postoperative care and follow-up will be blinded to treatment allocation, until the process of unblinding.

### Procedure for unblinding if needed {17b}

The unblinding process occurs at the 12-month follow-up if the patient wishes to be informed. However, in the case of severe adverse events necessitating unblinding before the 12-month follow-up, the project nurse, with access to the patient’s treatment allocation, will facilitate the unblinding process.

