### Follow-up

In this trial, patients will attend outpatient visits with clinical exams, blood samples, Duplex ultrasound (DUS), and quality of life (QoL) questionnaire at 6 weeks, 12 months, and then annually to 5 years postoperatively. CTA will be performed once at 12 months postoperatively, prior to the scheduled follow-up. In case of prohibitive traveling distance to the study site, the follow-up DUS at 1 year and beyond can be omitted from the protocol and replaced by CTA at investigators discretion. As the primary study endpoint is at 1 year, this alteration will not interfere with the conclusions. If there is suspicion of an in stent re-stenosis based on the clinical exam and DUS of the SMA (threshold 412 cm/s) [6], a patient will undergo a CTA. Following evaluation of CTA results and clinical examination, the patient may be offered additional treatment if indicated.

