## Statistical methods

### Statistical methods for primary and secondary outcomes {20a}

Outcomes are analyzed on intention to treat basis and secondarily per protocol. Primary outcomes will be analyzed by *t*-test and overall survival analysis, to estimate the patency at 12 months.

Secondary endpoints will be analyzed by survival analysis techniques, such as Kaplan–Meier curve and log-rank tests. ANOVA repeated measures will be used to estimate comparison QoL between the two groups, and secondary stent patency. Log-rank test will be used to compare the survival rates between groups. Sensitivity and specificity of CTA and US will be analyzed with a logistic regression and receiver operator curves (ROC) analysis.

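### Optional unblinding at the 12-month visit, worded so that the follow-up physicians' blinding ends with it, leaves the year 2 to 5 quality-of-life, symptom and reintervention comparisons partly open-label

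*Protocol article*

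**What the plan says.** Two adjacent sections of the protocol article govern blinding. Under Who will be blinded {17a}: "Patients and the physicians responsible for postoperative care and follow-up will be blinded to treatment allocation, until the process of unblinding". Under Procedure for unblinding if needed {17b}: "The unblinding process occurs at the 12-month follow-up if the patient wishes to be informed". Section {17b} also has a safety route, "in the case of severe adverse events necessitating unblinding before the 12-month follow-up, the project nurse, with access to the patient’s treatment allocation", through which the allocation can be disclosed earlier.

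Follow-up runs well past that point. The secondary endpoints are "evaluated at 12 months and 5 years", and they include quality of life, symptom recurrence, reintervention and intervention-free survival. The Follow-up section schedules the clinical examination, blood samples, duplex ultrasound and "quality of life (QoL) questionnaire at 6 weeks, 12 months, and then annually to 5 years postoperatively". It places the single scheduled postoperative CTA at 12 months, ahead of that visit. Further treatment may be offered after a clinical examination and CTA have been evaluated.

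**The concern.** The two blinding sections share one end point. Section {17a} ties the blinding of patients and of follow-up physicians to the same process, and {17b} places that process at the 12-month visit for any patient who wants to know. Read together, a patient's request can end the blinding of the physicians who examine that patient for the next four years. Granting the request does not require this.

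The exposed endpoints are those most open to knowledge of the allocation. EQ-5D-5L, SF-36 and symptom recurrence depend on what the patient reports. Reintervention and intervention-free survival depend on a clinician's decision, reached through examination, suspicion and further imaging. In the modified timeline (Table 2), years 2 to 5 consist of questionnaires and a telephone consultation, so the evidence there is mainly self-report.

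Patients also select themselves into unblinding after randomisation, possibly because of how they feel. Each arm would then mix blinded and unblinded patients, and a later comparison restricted to those still blinded would not be a randomised one. A difference at 5 years could partly reflect expectation or a changed threshold for action rather than the stent.

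**Working it through.** **Inputs from the protocol article**
- Post-baseline visits (Follow-up; Tables 1 and 2): 6 weeks, 12 months, and 2, 3, 4 and 5 years, 6 in all.
- Routine unblinding ({17b}): at the 12-month visit, on request.
- Sample size ({14}): 49 per arm, 98 in total; rates 0.85 and 0.60, alpha 0.05, power 0.80.

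**The plan's own figure.** Two-sided test of two proportions, pooled variance under the null, no continuity correction; mean proportion (0.85 + 0.60)/2 = 0.725:

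n = [1.960·√(2 × 0.725 × 0.275) + 0.842·√(0.85 × 0.15 + 0.60 × 0.40)]² / 0.25² = (1.238 + 0.510)² / 0.0625 ≈ 48.9, rounded up to 49 per arm.

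The stated figure reproduces (power at 49 per arm 0.801). The blinding rule does not affect it. It is used below only as the group size.

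**Share of visits after the unblinding point.** Years 2, 3, 4 and 5 follow it: 4/6 = 67%. If a proportion u of patients ask, the unblinded share of all post-baseline visits is u × 4/6. The document does not give u, so the whole range is shown.

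| u (assumed) | patients of 98 | share of post-baseline visits unblinded |
|---|---|---|
| 0% | 0 | 0% |
| 25% | about 24 | 17% |
| 50% | 49 | 33% |
| 75% | about 74 | 50% |
| 100% | 98 | 67% |

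The share exceeds one half only if u × 4/6 > 1/2, that is, u > 75%.

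**Illustrative effect on a quality-of-life comparison.** Assume no true difference, and that knowing the allocation moves reported scores by d SD between the arms. For a two-sided z-test at 5% with 49 per arm, the non-centrality is λ = d / √(2/49) = d / 0.202, and the rejection rate is Φ(−1.96 + λ) + Φ(−1.96 − λ). If only half the patients are affected, the average shift is d/2.

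| d (assumed) | all affected: λ | rate | half affected: average shift | λ | rate |
|---|---|---|---|---|---|
| 0.1 | 0.495 | 7.9% | 0.05 | 0.247 | about 6% |
| 0.2 | 0.990 | 16.8% | 0.10 | 0.495 | 7.9% |
| 0.3 | 1.485 | 31.8% | 0.15 | 0.742 | about 11.5% |

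The shifts are assumptions; the document gives no basis for their size. The calculation is for a single late time point. The planned repeated-measures ANOVA ({20a}) also uses the 6-week and 12-month data, which would dilute a shift confined to years 2 to 5. The calculation does not cover symptom recurrence or reintervention.

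**The case against.** The strongest reply is that the rule is narrower than it may look. Unblinding is conditional on the patient's wish, so a reader who infers that blinding ends for everyone at 12 months goes beyond the text: a patient who does not ask stays blinded. Section {17b} speaks only of informing the patient, and {16a} and {16c} reserve the allocation for the treating team. That stands. The physicians' loss of blinding is an inference from {17a} read with {17b}. It is the plain reading of {17a}, however, and no sentence keeps them blinded after disclosure.

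A reader might also infer that most of the secondary evidence becomes open-label. The document does not support this. The secondary endpoints are also evaluated at 12 months, survival is not a matter of judgement, patency and restenosis rest on imaging thresholds, and uptake is unknown. Nor is the primary endpoint shown to be at risk, since the CTA comes before the visit.

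It is equally tempting to say that patients are told the covered stent is closer to guidelines. Section {18b} describes it in that way, but this is protocol text, and the list in {26a} of what patients are told does not include it. A favourable expectation among patients is possible but not documented.

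Finally, the order of assessments within a visit and the recording of unblinding dates are details that a condensed article may leave to the full protocol. Their absence is therefore not counted as an error here. The point rests on the stated end of blinding.

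**Conclusion.** The point holds as a limitation of the later secondary comparisons. As worded, {17a} and {17b} let a patient's request at 12 months end blinding for the patient and, on the plain reading, for the follow-up physicians, while self-reported and clinician-driven endpoints are compared for four more years. For patients who ask, 4 of 6 post-baseline visits are exposed; across the trial the share lies between 0% and 67% of visits, depending on an uptake that the document does not give.

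The false-positive rates are illustrations. Those for all patients affected are a ceiling for the assumed shifts, and those for half affected show how far partial uptake dilutes them. They also require that knowing the allocation acts differently in the two arms; an equal shift in both would cancel. The sample size and, largely, the primary endpoint are untouched. The change is worth making because it is cheap and because analysis cannot repair the bias afterwards.

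**What to change.** Amend {17a} and {17b} so that:

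1. a patient who asks is told the allocation only after the 12-month examination, ultrasound and questionnaires have been recorded;
2. disclosure is to the patient only, and follow-up physicians and outcome recorders stay blinded until the 5-year visit except where safety requires otherwise;
3. the date of each unblinding is recorded, and the year 2 to 5 quality-of-life, symptom and reintervention results are described as partly unblinded.

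Items 1 and 2 reduce the bias; item 3 alone would only document it. The cost is a few sentences and one date field in the database, with no change to sample size or treatment. The amendment can still help patients who have not yet reached 12 months or have not yet been unblinded. The small downside is that an informed patient may reveal the allocation to the physician, so protection after disclosure will be incomplete.
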